## Methods and analysis

### Design

An intervention development and feasibility study including focus group discussions, a historically controlled evaluation and process evaluation.^29 30^ The intervention is implemented in two antenatal care clinics in mid-Sweden. The feasibility and piloting includes testing procedures for acceptability, estimating the likely rates of recruitment and retention of women and the calculation of appropriate sample sizes for future controlled trials. Complex interventions that are adjusted to local, specific^31^ or personal needs^32^ are likely to be more effective than completely standardised models.^29^ Key principles underpinning the study are therefore:

Active involvement of Somali parents and midwives in needs assessment and care design.Attention to language and contextual factors.Flexibility in study methods to respond to issues as they arise.A care model ready to continue or be replicated after the project concludes with only minor adjustments.

Hooyo consists of four phases with process evaluation activities informing study progress. Phase I is the preparation phase, including needs assessment, the development of contextual understanding and building a logic model for the project. Phase II includes the development of the intervention and of the evaluation tools, and phase III involves implementation and evaluation of the intervention using historical controls. In phase IV, the implementation process, the feasibility and the mechanisms of impact are evaluated, including contextual factors, using Moore’s Process Evaluation of Complex Interventions as an overarching framework.^30^ Phases I and II were conducted in 2016–2017. Recruitment and data collection for the historically controlled evaluation (phase III) and process evaluation (phase IV) commenced in late 2016 and will be completed during 2020. Women in the control group were recruited between October 2016 and April 2018 and recruitment of women into the intervention began in May 2018 and will be complete in December 2019. Final data collection will be completed by July 2020. The paper covers methodological aspects of all four phases of the study.

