#### The intervention: gANC

The intervention consists of gANC offered at both sites, modified to the needs in each site and group. Women are allocated to a group with women at similar stages of pregnancy within a 4-week gestational age span. From the second visit (gestational weeks 20–26), they receive gANC. Each group will consist of six to eight women and partners (or another support person) for optimal group dynamics and dialogue. While reports of gANC internationally involve numbers in groups of 5–20 in low-income to middle-income countries^41^ and 8–12 in high-income countries,^42^ the need to provide interpreting during groups sessions led to the choice of a somewhat smaller group size as being appropriate to allow all group members a chance to participate in the discussions. Partners are generally encouraged to participate in Swedish ANC, and hence this will be the point of departure also for the gANC but with the final decision about partner participation taken by the women included in each group. Frequency and number of sessions follow the national Swedish programme for antenatal care, that is, eight to nine appointments during a normal pregnancy. Each visit includes a group session for 1 hour, facilitated by one of two midwives assigned to the group and with interpreter assistance. Although each group session has a focus on a theme related to pregnancy, birth or parenting in line with national recommendations,^17^ particular emphasis will be given to issues and questions raised by the participants. Group care allows women to talk with each other and share their experiences in their own language. They also hear midwives’ responses to other women’s questions, expanding the dialogue and information sharing that can occur between midwives and women. The presence of an interpreter facilitates communication between the women and the midwives.

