##### Outcome measures

Primary outcomes are women’s overall ratings of antenatal care and emotional well-being. Ratings of care are assessed by the core question ‘When thinking about your overall experience of antenatal care—in general, have you been happy with the care that you have received?’ with response alternatives always, mostly, sometimes, rarely and never. The question is modified from MFMCQ^43^ and more detailed questions about specific aspects of care are also included. Emotional well-being is assessed with EPDS, completed in English, Swedish or Somali as appropriate.^45^

Secondary outcomes are adequate number of visits measured by the Adequacy of Prenatal Care Utilization Index, that is, expected number of visits in relation to actual number adjusted for gestational week at booking visit and delivery,^47^ social support during pregnancy using slightly modified questions from the Pregnancy Risk Assessment Monitoring System^48^ and worries about the upcoming birth using questions from the Cambridge Worry Scale.^44^ Knowledge about danger signs and where to seek healthcare if particular symptoms arise are assessed by questions with multiple choice responses, such as ‘Now at the end of your pregnancy, where would you turn if you had bleeding from the vagina? When would you seek care?’. From the patient record, the following are retrieved: estimated time spent with the antenatal care midwife, gestational age at the first ANC visit, lowest measurements of haemoglobin and S-ferritin, weight gain, attendance at parent education, mode of birth, interventions (induction of labour, pain relief including epidural, oxytocin), blood loss, diagnoses (mother) and gestational age, birth weight, Apgar score, umbilical cord pH and the need for neonatal intensive care (infant).

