#### Data collection for the intervention

##### Questionnaires

Questionnaire data are collected at three time points (Q1, Q2, Q3). The baseline measurement (Q1) is conducted after recruitment, that is, before gestational week 25. Women are contacted for a face-to-face or telephone structured interview in Somali, Swedish or English at a place of their choice. Q1 includes questions on background (parity, education, income, occupation), migration (time of residence, reason for migration, migration status, language) and social support, psychological and physical well-being, knowledge of danger signs and the health system and expectations about the upcoming birth. Data for Q2 are collected in late pregnancy, after gestational week 35, in the same manner. Q2 includes questions on experiences of care and information during the ongoing pregnancy, knowledge of the health system, pregnancy and birth, social support and psychological and physical well-being and expectations for the upcoming birth. Q3 is administered 2 months postpartum and includes questions regarding the overall experience of pregnancy, ANC, birth and psychological and physical well-being. After each interview, a small gift is offered as a token of appreciation for women’s participation.

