#### Sample size issues

Our main purpose is to develop and test the feasibility of the intervention and study processes and in so doing, also provide information to inform sample size calculations for possible future randomised controlled trials. Nevertheless, based on available birth rate data, we estimate being able to include 100 women in the control group and 100 women in the intervention group during the study period. We estimate that the study will have the power to detect a clinically relevant increase in women’s overall satisfaction with antenatal care from an expected 65% among Somali women receiving individual care to 82% in those receiving gANC (approximating rates for Swedish speaking women in a national population based study^50^ with 80% power and an alpha of 20%, with 70 women in each group). To have similar power to detect differences in mean scores on the Edinburgh Postnatal Depression Scale (a hypothesised reduction from a mean of 8.0 in the control group— similar to that found in studies of migrant women, to 6.0 in the gANC group—similar to that found in Swedish population-based studies,^51^ 63 women are required in each group. Allowing for 20% loss to follow-up at the time of data collection with women 2 months postpartum, 174 women will need to be recruited.

Differences between groups will be described as ORs and 95% CIs after estimation by means of logistic regression analyses. Comparison of means will be undertaken using t-tests where data are normally distributed or medians compared using Mann-Whitney U tests if not.

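### The co-primary EPDS comparison with historical controls is fixed as an unadjusted t-test or Mann-Whitney test, so measured case-mix and site-mix differences between the two periods stay in the estimate

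*Protocol article*

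**What the plan says.** Under Outcome measures the protocol article states: "Primary outcomes are women’s overall ratings of antenatal care and emotional well-being". It adds: "Emotional well-being is assessed with EPDS". The sample size section treats the EPDS as a difference in mean scores, 8.0 under individual care against 6.0 under group care, with 63 women per group.

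The comparison is not randomised. The Design section says that "phase III involves implementation and evaluation of the intervention using historical controls", and gives the dates: "Women in the control group were recruited between October 2016 and April 2018 and recruitment of women into the intervention began in May 2018". The recruitment periods do not overlap.

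The analysis text is the last paragraph of Sample size issues. Differences between groups are to be given as odds ratios with 95% confidence intervals from logistic regression, with no covariates named. For means it says: "Comparison of means will be undertaken using t-tests where data are normally distributed or medians compared using Mann-Whitney U tests if not".

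The baseline questionnaire already holds what an adjusted analysis would need: "Q1 includes questions on background (parity, education, income, occupation), migration (time of residence, reason for migration, migration status, language) and social support". The same sentence goes on to psychological and physical well-being. No adjustment, matching, weighting or treatment of period differences is described anywhere in the article.

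**The concern.** With historical controls, the difference in mean EPDS contains the effect of group care plus every other difference between the women recruited in the two periods. The article itself gives reasons to expect such differences:

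- At site 1 the Somali population had grown fivefold in a decade, and many women were not yet fluent in Swedish.
- At site 2 Somali-born residents had lived in the area for more than 25 years, and midwives reported that most could communicate in Swedish.
- A shift in the share of women from each site, or in length of residence within site 1, would therefore change case mix between periods.

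The article also notes that person-centred care was being introduced across the health system at the same time. The stated limitations mention two sites and one immigrant group, but not confounding by period.

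This is more than detail left to a fuller document. The article names the method for means, and that method cannot use the baseline data. At stake are the estimate for a co-primary outcome and the figures passed on to the sample size of a later randomised trial, which is a declared purpose of the study.

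**Working it through.** **1. The plan's own figures.** The article gives no SD for the EPDS, so 63 per group cannot be reproduced from its inputs alone. With n = 2·SD²·(z_α + z_β)²/δ², δ = 2.0 and 80% power:

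- Two-sided 5% with SD 4.0: 2 × 16 × (1.960 + 0.842)²/4 = 62.8, so 63.
- Two-sided 20%, solved for SD: √[63 × 4/(2 × (1.282 + 0.842)²)] = 5.29.

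The only alpha stated is 20%, given for satisfaction, and its sidedness is not stated. For satisfaction (65% against 82%), two-sided 20% gives 60 per group, or 72 with continuity correction, against the stated 70. Allowing 20% loss, 140/0.8 = 175 against the stated 174. None of these figures is in dispute here.

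**2. What a difference between periods does to the unadjusted test.** Assumptions: no effect of group care, 70 women analysed per group, two-sided 5% (matching the 95% intervals the article plans for odds ratios), and SD 4 to 5, since none is stated. Let b be the difference in mean EPDS between periods from any cause other than group care.

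SE = SD × √(2/70). P(significant) = Φ(b/SE − 1.96) + Φ(−b/SE − 1.96).

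- SD 4.0: SE = 0.676. For b = 1, b/SE = 1.479 and P = 0.316.
- SD 5.0: SE = 0.845. For b = 1, b/SE = 1.183 and P = 0.219.

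| b (EPDS points) | SD 4.0 | SD 5.0 |
|---|---|---|
| 0 | 5% | 5% |
| 0.5 | 12% | 9% |
| 1.0 | 32% | 22% |
| 1.5 | 60% | 43% |
| 2.0 | 84% | 66% |

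At SD 5.29, b = 1 gives b/SE = 1/0.894 = 1.118 and P = 0.20. The conclusion does not depend on which SD lies behind 63.

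**3. Whether adjustment costs precision.** With SD 4.0 and an assumed baseline–outcome correlation r, n scales by 1 − r²: 62.8 × 0.91 = 57.1, so 58 at r = 0.3; 62.8 × 0.75 = 47.1, so 48 at r = 0.5. The required n does not rise. This ignores imbalance of covariates between groups, which takes back some of the gain.

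**4. How many covariates the satisfaction model can carry.** At the plan's rates with 70 per group, women not counted as satisfied number 70 × 0.35 + 70 × 0.18 = 24.5 + 12.6 = 37.1. Group plus six covariates is at least 7 parameters, or 37.1/7 = 5.3 such women each. Group plus three is 4 parameters if each is a single term, or 37.1/4 = 9.3 each.

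**The case against.** The strongest reply is that this is a feasibility study. The article gives development and feasibility as its main purpose, discloses the historical controls openly, and compresses the analysis into two sentences. The sentence on means does not name the EPDS, and logistic regression, planned for differences between groups, can take covariates. This lowers the weight of the point without removing it. The EPDS is a declared primary outcome, it is sized on means, and the only method given for means cannot be adjusted. The absence of named covariates in the logistic model is not itself held against the article.

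It can also be said that the size rests on assumptions. That stands: the documents give no SD and no evidence that the periods differ by any particular amount.

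Four stronger readings are tempting, and the documents do not support them:

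- **That regression would remove the calendar-period problem.** It addresses measured characteristics only. A real change in care or context between the periods would remain.
- **That baseline data are contaminated by group care.** One section says "The baseline measurement (Q1) is conducted after recruitment, that is, before gestational week 25" and another says "From the second visit (gestational weeks 20–26), they receive gANC", so overlap is possible on paper. But women are contacted after the first antenatal visit and groups begin at the second, so the ordinary order is questionnaire first. The logic model also starts groups from week 24, which would leave only about a week of overlap.
- **That 63 per group implies an SD of 4, making normality untenable.** SD 4 requires a two-sided 5% alpha that the article does not state. With about 70 per group a t-test also tolerates moderate skew. The loose wording on Mann-Whitney and medians is a minor matter.
- **That a baseline EPDS score is certainly available.** The baseline questionnaire is said to cover psychological well-being, without naming the EPDS.

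**Conclusion.** The point holds in a limited form. As written, the comparison of means, and so the co-primary EPDS comparison, is unadjusted between two non-randomised consecutive cohorts, although the baseline data that would allow adjustment are already collected. Measured case-mix and site-mix differences therefore go into the estimate.

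The size is illustrative. With SD 4 to 5, 70 per group and a two-sided 5% test, a 1-point difference between periods (half the hypothesised effect) gives a significant result in about 22% to 32% of studies with no effect of group care. That figure covers differences from any cause, and adjustment can remove only the part carried by measured covariates. The feasibility purpose makes this a flaw in how one outcome is analysed, not a reason to reject the study.

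**What to change.** 1. Make the main EPDS comparison a linear regression with robust standard errors, and report the adjusted mean difference with its 95% confidence interval. Adjust for the baseline well-being score (baseline EPDS if collected), site, parity, time of residence, language and education. Name the EPDS time point to which it applies.
2. Keep the unadjusted t-test or Mann-Whitney test as a supporting analysis.
3. For satisfaction, use the planned logistic model with a small prespecified covariate set, for example site, parity and time of residence. About 37 non-satisfied women will not support the full list.
4. State in the analysis text and the limitations that adjustment addresses measured case mix only and cannot separate group care from secular change between 2016–18 and 2018–19.

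The cost is a change of wording and slightly more analysis work. No new data items or participants are needed. The drawback is dependence on complete baseline covariates, so the handling of missing values should be settled before the analysis.

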### Phase IV: design of the process evaluation

A process evaluation using a mixed methods approach will be conducted throughout the study.^29^ The process evaluation will address whether the intervention was carried out according to plan, what was achieved, if and what adaptations were needed, who was reached by the intervention, any unexpected events and will also aim to understand the mechanisms of impact and what mediated these mechanisms. The process evaluation will also address contextual factors.^30^

#### Process evaluation data collection and measures

Data collection for the process evaluation^30^ will be nested in the different phases, supported by different measurement tools and activities. Moore’s process evaluation framework^30^ will guide the data collection, analysis and interpretation. The framework emphasises the impact of, and relationship between the intervention, implementation, mechanisms and context, and a topic guide and analysis will focus on what is achieved and how (fidelity, dose, adaptations, reach). Focus for the mechanisms of impact will be the participants’ interactions with the intervention and potential mediating factors.

A session checklist for completion by the midwife after each group session will cover topics discussed, resources used, number of participating women and support people, group dialogue and the midwife’s brief view of each session. The checklist was developed by the research team, discussed with the reference group and, after adjustments, presented to all included midwives for further modifications, which were addressed by the researchers before intervention start.

Participant observations during the group sessions will contribute data describing the delivery of gANC and the mechanisms of impact by describing group dynamics, dialogue and active participation by women in group sessions. A protocol for observations during group sessions developed by the research team, focuses on group mechanisms, dialogue and interaction, based on PPC and MI principles. This will provide the guide for participant observations by one or two members of the research team during a number of randomly selected group sessions.

Participant experiences of group antenatal care: Questionnaire data for all participating women and qualitative data collected from women, midwives, partners, interpreters and heads of departments will describe responses to and interactions with the intervention and their views regarding the feasibility of the intervention and mechanisms of impact. Women’s experiences of the content, structure and feasibility of gANC will be assessed in the follow-up questionnaire (Q3) at 2 months postpartum. Additionally, the questionnaires will identify a sample of women with a diversity of experiences to be recruited for more in-depth individual interviews. Midwives’ experiences of the same, and their perceptions regarding mechanisms of impact will be collected through qualitative FGDs or interviews as appropriate. Partners’ and interpreters’ views will be collected through qualitative individual interviews on completion of participation. FGD and interview data will be collected using a topic guide with open-ended questions developed by the research team and analysed using deductive content analysis according to Elo and Kyngas.^52^ Field notes taken by the researchers in dialogue with research assistants, involved midwives and heads of departments will assist in describing the choices and decisions made during the implementation process.

### Patient and public involvement

The initial literature review informing the research questions included studies focusing on immigrant women’s experiences and views of maternity care postmigration, including the views of Somali-born women. Initial focus group discussions for the study included Somali women and men with recent experiences of antenatal care, and these informed the development of the intervention. As described above, a study reference group involves Somali community members in all stages of the project, and a bicultural research assistant is involved in recruiting women to the study. All participants will receive a summary of the results in their preferred language, and seminars will be held with stakeholder groups.

## Discussion

The Hooyo study is an attempt to address some of the health and care disparities in the Swedish antenatal care system. The development and feasibility design of the study,^29^ together with the nested process evaluation,^30^ will contribute valuable information for future randomised controlled studies, as well as in the design of antenatal care interventions focused on reducing inequalities in health between immigrants and non-immigrants. The study will provide guidance on the acceptability of this model of care among Somali-born women, their partners and midwives in Sweden and on recruitment and data collection from responders who are often excluded from research due to communication barriers or marginalisation. The study will also indicate whether gANC has a positive impact on Somali women’s experiences of antenatal care and might therefore be appropriate for other migrant groups.

For the midwives, the intervention provides a platform for reflection and dialogue about improving care for migrant women. This is vital, since care provision is always an interplay between caregivers and care receivers. The early inclusion of midwives’ and participants’ views provided space to shape the planned intervention in relevant ways in terms of content, structure and underlying core principles.^32^ By emphasising dialogue, a person-centred approach and the active participation of women, partners and midwives throughout development and implementation of the intervention, we hope to develop a relevant, pragmatic and acceptable model of care for this group of immigrant women, and one that might replicate well to other settings and groups with minor adjustments. The challenge is to develop and implement an acceptable model of care addressing diverse needs of the care-receiving group and suited to local conditions, while ensuring that medical and public health guidelines are fulfilled. The findings of the study will determine if this can be achieved.

It could be argued that the study should include more antenatal care sites and a range of different immigrant groups. Funding limitations meant restricting the study to two sites and focusing on only one immigrant group, something that may limit the study’s generalisability. On the other hand, it is expected that many of the strategies employed to develop and test group antenatal care in this study, and the lessons learnt in doing so, will have future relevance in improving antenatal care for immigrant women more generally.

